**No non-FDA drugs will be administered. The CT scans are expected to be without iodinated contrast agents.**

Date: ____________________

Principal Investigator: _________________

Application Number: ___________

1. **Study Statistics**
2. Primary outcome variable.
3. Secondary outcome variables.
4. Statistical plan including sample size justification and interim data analysis.

This is a pilot study involving 10 patients and hence there are no interim data analysis or conflicts regarding sample size. Descriptive data will be outlined for all the participants tabulating the variables as determined. The intrapatient variability as well as accuracy and precision of the device will be obtained individually for Group I and Group II patients. The correlation (non-parametric) Spearman correlation coefficient will be obtained to assess the relationship between the uptake and findings as obtained by the collar device and conventional methods of uptake measurement.

1. Early stopping rules.

Early Stopping Rules Include but not limited to:

1. Severe, unexplained discomfort with the device. (2) Lack of device tolerability or interference with optimal functioning of daily activity (3) Discomfort after stopping anti-thyroid treatments causing rebound hyperthyrodism
2. **Risks**
3. Medical risks, listing all procedures, their major and minor risks and expected frequency. b Steps taken to minimize the risks.

The following risks are anticipated:

• Pressure sensation and possible skin irritation due to compression of skin around the neck. The patients can remove the collar for a few hours every day to avoid this.

• Transient redness around the neck if the collar is placed too tightly.

• For persons with prior thyroid surgery, the device might give cause an unpleasant rubbing sensation, especially if the surgical scar is very fresh.

• Rarely, it could cause patients to experience discomfort with swallowing, but the patients will be given all the necessary information to prevent this. If the participants feels uncomfortable, he/she can remove the device anytime

• The participants will also receive 1-4 low-dose CT scans. The cumulative radiation doses will be very low. Radiation imposed minimal risk at very low doses.

- The participants will undergo a low dose 0.2 mci I-131 dosing that is not associated with thyroid “stunning” and is much less than the 12 mCI (about 60 times 0.2) that they will receive for theraupetic treatment of graves disease

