1. Plan for reporting unanticipated problems or study deviations.

If there are unanticipated problems, there will be a documentation as per the IRB rules and incident report guidelines. If there are severe unanticipated problems, the study would be discontinued.

1. Legal risks such as the risks that would be associated with breach of confidentiality.

Legal risks include;

- Breach of confidentiality
- Damage to device and lack of compensation for it
- Risks associated with performing a CT scan

1. Financial risks to the participants.

The medical cost of injury due to unanticipated events during the course of the study

Data and Safety Monitoring Plan:

Routine and continuous monitoring for human subject safety events will be undertaken by the Principal Investigator. In addition, the PI, working with the study staff, will oversee the progress of the study and review participant data for untoward events that are anticipated or unexpected.

Adverse events will be reviewed promptly and assessed for trends or to isolate risks not previously identified. Any serious adverse events will be communicated to the IRB per JHMI IRB policies.

1. **Benefits**
2. Description of the probable benefits for the participant and for society.

This study will apply a novel “wearable” radiation detection technology to determine continuous cervical measurements over days following tracer radioiodine administration will provide information that permits the tailoring of subsequent therapeutic radioiodine doses more precisely to improve clinical outcomes, as described above.

The project aims to explore a promising technology for individualizing therapy by assessing the individual variability in the I-123/I-131-time activity curves, minimizing the risk of 131-I administration while achieving highest possible cure rates by tailoring the I-131 dose and lower the need for frequent follow up visits -laboratory and imaging evaluation and health care costs overall.

1. **Payment and Remuneration**
2. Detail compensation for participants including possible total compensation, proposed bonus, and any proposed reductions or penalties for not completing the protocol.

The participants will be compensated with a gift card of 25 USD per visit that is part of the research. The standard of care visits will not be compensated. At the end of the 7 days period,the participants will receive a 50 USD for compliance and completion.

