There are no penalties for completing the protocol except that the gift cards will have to be returned back.

1. **Costs**
2. Detail costs of study procedure(s) or drug (s) or substance(s) to participants and identify who will pay for them.

The study is being funded by a small grant received by the Thyroid Tumor Center (under the stewardship of [name]) that is a subsidiary of the Division of Endocrinology, Department of Medicine, Johns Hopkins Hospital.

|  |  | ***Run-***  ***Up-days***  ***0*** | ***Day 0***  ***9.00 am*** | ***Day 0***  ***3 pm*** | ***Day 1***  ***9 am*** | ***Follow up***  ***Day***  ***7*** |
| --- | --- | --- | --- | --- | --- | --- |
|  |  | ***-4 ± 1*** |  |  |  |  |
| ***Stop anti-thyroid meds*** | | ***X*** |  |  |  |  |
| ***I-123 dose*** | |  | ***X*** |  |  |  |
| ***COTI measurement*** | |  | ***X0*** | ***X0*** | ***X0*** |  |
| ***Uptake Measurement by probe (SOC)*** | |  | ***X*** | ***X*** | ***X*** |  |
| ***I-123 Planar scan*** | |  |  | ***X*** |  |  |
| ***Informed Consent*** | |  | ***X0*** |  |  |  |
| ***Review Eligibility*** | |  | ***X0*** |  |  |  |
| ***Medical History*** | |  | ***X*** |  |  |  |
| ***Physical Exam*** | |  | ***X*** |  |  |  |
| ***Vital Signs*** | |  | ***X*** |  |  |  |
| ***Clinical Labs*** | |  | ***X*** |  |  |  |
| ***Pregnancy Test-eligible*** | |  | ***X*** |  |  |  |
| ***Place Collar*** | |  | ***X0*** |  |  |  |
| ***Give instructions*** | |  | ***X0*** |  |  |  |
| ***Questionnaires*** | |  | ***X0*** |  |  |  |
| ***Adverse Events*** | |  | ***X0*** |  |  |  |
| ***Concomitant***  ***Medications*** | |  | ***X0*** |  |  |  |

***Table A Schedule of Visits after 123 dose for Graves disease Patients – All the visits marked with superscript (o)are part of research-Imaging schedule after I-123 dose***

|  | ***Visit***  ***No.*** | ***Run-***  ***up***  ***0*** | ***Day***  ***0***  ***9 am*** | ***Day***  ***1***  ***9 am*** | ***2***  ***9***  ***am*** | ***3***  ***9***  ***am*** | ***4***  ***9***  ***am*** | ***5*** | ***6*** | ***Follow-***  ***up***  ***7***  ***9am*** |
| --- | --- | --- | --- | --- | --- | --- | --- | --- | --- | --- |
| ***Activity*** | ***Days*** | ***-4 ± 1*** | ***0*** | ***1*** | ***2*** | ***3*** | ***4*** | ***5*** | ***6*** |  |
| ***Stop thionamide***  ***anti-thyroid meds*** | | ***X**** |  |  |  |  |  |  |  |  |
| ***I-131 200 µ administration*** | |  | ***X**** |  |  |  |  |  |  |  |

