| ***Uptake Measurement*** | |  | ***X**** | ***X**** |  |  |  |  |  |  |
| ***Informed Consent*** | |  | ***X**** |  |  |  |  |  |  |  |
| ***Review Eligibility*** | |  | ***X**** |  |  |  |  |  |  |  |
| ***Medical History*** | |  | ***X**** |  |  |  |  |  |  |  |
| ***Physical Exam*** | |  | ***X**** |  |  |  |  |  |  |  |
| ***Vital Signs*** | |  | ***X**** |  |  |  |  |  |  |  |
| ***Clinical Labs*** | |  | ***X**** |  |  |  |  |  |  |  |
| ***Pregnancy Test*** | |  | ***X**** |  |  |  |  |  |  |  |
| ***Place Collar*** | |  | ***X**** |  |  |  |  |  |  |  |
| ***Give instructions*** | |  | ***X**** |  |  |  |  |  |  |  |
| ***Questionnaires*** | |  | ***X**** | ***X**** |  |  |  |  |  |  |
| ***SPECT $*** | |  | ***X* 3pm*** | ***X**** | ***X**** | ***X**** |  |  |  |  |
| ***COTI measurement$*** | |  | ***X* 3pm*** | ***X**** | ***X**** | ***X**** | ***X**** |  |  |  |
| ***Low dose CT for attenuation correction*** | |  |  | ***X**** |  |  |  |  |  |  |
| ***Adverse Events*** | |  | ***X**** | ***X**** |  |  |  |  |  |  |
| ***Medications*** | |  | ***X**** | ***X**** |  |  |  |  |  |  |

***Table B- Imaging schedule for Graves disease low dose I-131 scan, COTI measurement and SPECT CT at 3 pm that day-The schedule marked with superscript are part of the research.This is a research scan.***

| ***SCHEDULE OF PROCEDURES*** | | | | | | | | | | | |
| --- | --- | --- | --- | --- | --- | --- | --- | --- | --- | --- | --- |
|  | ***Visit***  ***No.*** | ***Run-***  ***up***  ***0*** | ***Day***  ***1***  ***Time***  ***9.00 am*** | ***2***  ***9***  ***am*** | ***3***  ***9 am*** | ***4***  ***9 am*** | ***5***  ***9***  ***am*** | ***6*** | ***7*** | ***8*** | ***Day***  ***11*** |
| ***Activity*** | ***Days*** | ***-4 ± 1*** | ***0*** | ***1*** | ***2*** | ***3*** | ***4*** | ***5*** | ***6*** | ***7*** |  |
| ***Low iodine diet*** | | ***-14 +/-1 day*** |  |  |  |  |  |  |  |  |  |
| ***Informed Consent*** | |  | ***X*** |  |  |  |  |  |  |  |  |
| ***Review Eligibility*** | |  | ***X1*** |  |  | ***X1*** |  |  |  |  |  |
| ***Medical History*** | |  | ***X1*** |  |  |  |  |  |  |  |  |
| ***Physical Exam*** | |  | ***X1*** |  |  |  |  |  |  |  |  |
| ***Vital Signs*** | |  | ***X1*** |  |  | ***X1*** |  |  |  |  |  |
| ***Clinical Labs*** | |  | ***X1*** |  |  |  |  |  |  |  |  |
| ***Pregnancy Test*** | |  |  | ***X1*** |  |  |  |  |  |  |  |
| ***Thyrogen Injection*** | |  | ***X1*** | ***X1*** |  |  |  |  |  |  |  |

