| ***Diagnostic I-123 dose (1 pm)*** | |  |  | ***X1*** |  |  |  |  |  |  |  |
| ***Diagnostic WBS (11 am)*** | |  |  |  | ***X1*** |  |  |  |  |  |  |
| ***I-131 30 mci (1PM)*** | |  |  |  |  | ***X1*** |  |  |  |  |  |
| ***Give instructions*** | |  | ***X1*** |  |  |  |  |  |  |  |  |
| ***Questionnaires*** | |  | ***X1*** |  |  |  |  |  |  |  |  |
| ***COTI placement*** | |  |  |  |  | ***X*** |  |  |  |  |  |
| ***COTI measurement*** | |  |  |  |  | ***X*** | ***X*** | ***X*** | ***X*** | ***X*** | ***X*** |
| ***SPECT*** | |  |  |  |  |  | ***X*** | ***X*** | ***X*** |  | ***X1*** |
| ***Low dose CT for attenuation*** | |  |  |  |  |  | ***X*** |  | ***X*** |  | ***X1*** |
| ***Review of Risks***  ***Benefits*** | |  | ***X*** |  |  |  |  |  |  |  |  |
| ***Adverse Events*** | |  | ***X1*** | ***X1*** |  | ***X1*** |  |  |  |  |  |
| ***Concomitant***  ***Medications*** | |  | ***X1*** | ***X1*** |  | ***X1*** |  |  |  |  |  |

***Table C -Thyroid Cancer Patients-The events not marked with a superscript 1 are part of research. The events in red are part of research protocol. Imaging and visit schedule for thyroid cancer***

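### Scheduled adverse-event collection ends on the collar placement day (Tables A and C) or one day later (Table B), while collar readings continue for up to seven days after placement

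*Protocol*

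**What the plan says.** The three schedules at the end of the Protocol fix when adverse events are collected.

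- **Table A (Graves, I-123).** The adverse-event row is "Adverse Events* | | | *X0", a single mark at Day 0, 9 am. The collar is placed at that same visit ("Place Collar* | | | *X0") and read three times, to Day 1 ("COTI measurement* | | | *X0* | *X0* | *X0").
- **Table B (Graves, low-dose I-131).** The adverse-event row is "Adverse Events* | | | *X | *X", that is, Days 0 and 1. The collar is placed on Day 0 ("Place Collar* | | | *X") and read on Days 0 to 4.
- **Table C (thyroid cancer).** The adverse-event row is "Adverse Events* | | | *X1* | *X1* | | *X1", that is, Days 1, 2 and 4. The collar is placed on Day 4 and read on Days 4 to 8 and on Day 11.

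Other parts of the Protocol rely on what happens during wear. The Risks section lists pressure, skin irritation, redness and swallowing discomfort, and says that after thyroid surgery "the device might give cause an unpleasant rubbing sensation, especially if the surgical scar is very fresh". The early stopping rules under Study Statistics include severe discomfort and intolerance of the device. The Data and Safety Monitoring Plan gives the investigator ongoing safety surveillance and states: "Adverse events will be reviewed promptly and assessed for trends or to isolate risks not previously identified". The third aim in the Abstract is to assess patients' experience of the collar, including discomfort, by survey.

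**The concern.** The harms the Protocol expects from the device can occur only once the collar is on. The schedule asks about adverse events mostly before or at placement and hardly at all afterwards. A site that follows the tables exactly would have no scheduled enquiry after the placement day for Group II, who have all had a total thyroidectomy, and none after Day 1 in Table B.

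Three things depend on those data: the discomfort and tolerability stopping rules, the promised review for trends, and the third aim. This is a proof-of-principle study for a possible larger trial, so an incomplete tolerability record would be carried into that trial's planning. Visit schedules belong in the protocol, so this is not a detail that can be left to a statistical analysis plan.

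**Working it through.** No sample size or error rate is involved. The check is a column-by-column comparison of four rows in each table.

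**Alignment of Table C.** Table C has two header lines that differ by one day; the upper line is used here. The I-131 dose then falls under Day 4, which agrees with the Group II preparation text. Placement falls in the same column. Day 11 − Day 4 = 7 days, which agrees with the final image planned for day 7 after therapy.

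| | Table A | Table B | Table C |
|---|---|---|---|
| Collar placed | Day 0, 9 am | Day 0 | Day 4 |
| Collar read | Day 0 9 am, Day 0 3 pm, Day 1 | Days 0, 1, 2, 3, 4 | Days 4, 5, 6, 7, 8, 11 |
| Adverse events marked | Day 0, 9 am | Days 0, 1 | Days 1, 2, 4 |
| Questionnaires marked | Day 0, 9 am | Days 0, 1 | Day 1 |
| Reading visits after placement day | 1 | 4 | 5 |
| of these, with an adverse-event mark | 0 | 1 | 0 |
| Last adverse-event mark to last reading | about 1 day | 4 − 1 = 3 days | 11 − 4 = 7 days |

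**Readings after the placement day.** 1 + 4 + 5 = 10 visits, of which 0 + 1 + 0 = 1 has an adverse-event mark.

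**All readings, placement day included.** 3 + 5 + 6 = 14 visits. Those without an adverse-event mark number 2 (A), 3 (B) and 5 (C), so 10 of 14.

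**Sensitivity to the Group II text.** The imaging-times section lists Group II collar counts at 24, 48 and 96 hours and day 7, without 72 hours. On that list Table C has 4 later readings instead of 5, and the total becomes 1 of 9. The conclusion does not change.

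**Could another row fill the gap?** The questionnaire marks sit in the same early columns. In Table C the only one is on Day 1, 4 − 1 = 3 days before the collar is placed. The Day 7 follow-up columns of Tables A and B have no entry in any row.

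**Are the patients there to be asked?** Imaging or a probe uptake coincides with the later readings on Day 1 in Table A, on Days 1 to 3 in Table B, and on Days 5, 6, 7 and 11 in Table C: 1 + 3 + 4 = 8 of the 10. The other two, Day 4 in Table B and Day 8 in Table C, are readings only.

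**The case against.** The strongest reply is that adverse-event capture is not confined to the marked cells. The Data and Safety Monitoring Plan commits the investigator to ongoing monitoring, patients receive contact details for reporting discomfort, they may take the collar off at any time, and anyone who cannot wear it for the required period is removed. Serious intolerance would probably come to light. The study has 10 patients, the collar delivers no energy, its readings do not set treatment doses, and the listed device harms are local. All of this stands and limits the weight of the point. It does not answer it, because none of these routes sets a time at which the patient is asked.

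Some stronger readings are tempting, but the documents do not support them:

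- **That the harms accumulate with wear.** The Risks section ties irritation to compression, redness to a tight fit, and rubbing to a fresh scar. It does not say they grow over time, and some could appear on the placement day.
- **That Group II has seven days of wear with no adverse-event check.** There is a mark on the placement day, and the table does not say whether it comes before or after fitting. Continuous wear is not established either: patients may remove the collar for some hours daily and no removal day is given.
- **That a low adverse-event count would be an artefact.** The Protocol proposes no adverse-event rate.
- **That Table C contains no research adverse-event assessment.** Its marks carry the superscript for non-research items, but the legend also relies on red type, which is not visible in the text at hand.

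**Conclusion.** The point holds as a mismatch between the visit schedules and the Protocol's own safety commitments. Scheduled adverse-event collection covers 1 of the 10 collar-reading visits after the placement day, and the last mark precedes the last reading by about 1 day (A), 3 days (B) and 7 days (C). Tables B and C carry the weight; in Table A the readings span only about 24 hours.

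The supported conclusion is that harms during wear are not collected at scheduled times. A reader might infer that they would not be collected at all, but the monitoring plan and the patient contact route rule that out. The kinetic comparison and the Spearman analysis are unaffected. What is weakened is the evidence for the tolerability stopping rules, the trend review and the third aim.

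This rests on the column alignment checked above and on taking the collar-reading visits as the best available guide to when the collar is worn.

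**What to change.** Mark Adverse Events at every existing collar-reading visit after placement in Tables A, B and C, including the last reading, and attach a short question on skin condition and neck comfort. For the later visits this means Day 1 in Table A, Days 2 to 4 in Table B (Day 1 is already marked), and Days 5 to 8 and Day 11 in Table C. The Day 0, 3 pm reading in Table A can carry the same mark. The schedules would then agree with the Risks section, the stopping rules, the monitoring plan and the third aim.

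The cost is a few minutes per existing visit and a minor amendment. If the two reading-only days (Day 4 in Table B, Day 8 in Table C) are not attended in person, which the Protocol does not state, the question could be put by telephone.

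Two extras are optional: a check in the Day 7 column of Tables A and B, which now holds no procedure and might add a contact, and an event rate per patient-day, which would need wear time to be recorded.
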